### 2.8. Sample Size Estimation

The study was designed as a feasibility study, preliminary to the conduction of a large-size efficacy trial. The size of an efficacy trial with breast cancer mortality (or incidence of metastatic breast cancer) as the primary endpoint should allow the observation of at least 380 events (breast cancer deaths, or incidence of metastatic breast cancer) in order to detect—with an 80% power—a 25% relative reduction in breast cancer mortality, which is considered the minimal effect of MRI screening that is worth detecting. Assuming a 60% survival at 10 years [27], and an average cumulative 10-year breast cancer risk of 5% (the lowest risk in this cohort should be about 3%) [22], we can estimate that at least 20,000 women followed for 10 years (with a further follow-up of breast cancers until 380 events have been observed) would be necessary for such an efficacy trial. However, accrual for large-size prevention trials is very difficult, as they target asymptomatic healthy individuals facing a variable but generally low risk. Thus, this feasibility trial aimed to estimate the sensitivity and specificity of MRI screening alone but also to provide information on the distribution of the risk profiles among enrolled women, as well as to estimate the sample size needed by an efficacy trial. Therefore, a planned enrollment of 2000 women (10% of the size of the efficacy trial) was proposed. Furthermore, organizational problems and quality control issues could be adequately addressed in a study of this size.

It can be expected that in this feasibility trial, over a 5-year screening period, about 40–60 cases of invasive breast cancer will be observed: one-third in the control arm; two-thirds in the MRI arm. These figures are close to those of previous uncontrolled MRI studies (e.g., the HIBCRIT study [15]) and would enable us to confirm the twofold increase in sensitivity associated with MRI. These figures were also considered sufficient to provide preliminary information on the MRI-associated lead time and on the stage distribution of incident breast cancers. Conversely, the number of advanced (metastatic or locally advanced) breast cancers and the number of breast-cancer-related deaths should be too small to allow any meaningful interpretation. Due to lead time, no effects of MRI on efficacy endpoints are expected to be noted during the first years. Any estimation of the proportion of interval cancers in each arm proved to be difficult, as this proportion is dependent on the age distribution of enrolled women.

Two and half years since the start of the study, when 1254 women had been randomized, enrollment stopped due to the end of the grant, and screening and diagnostic imaging was completed. A clinical follow-up of all randomized women is planned for at least 5 years.

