### 2.1. Study Design and Population

Women were randomly assigned to receive annual 2D MX plus US (standard-of-care arm) or MRI (experimental arm) with a 1:1 allocation ratio. Two screening rounds per woman were planned.

Women were deemed eligible for enrollment if aged 40–59 years and if they had a 15–30% BC-LTR and/or extreme BD on the most recent MX. BC-LTR was calculated using the IBIS Breast Cancer Risk Evaluation Tool version 6.0.0 (http://www.ems-trials.org/riskevaluator/, accessed on 30 August 2021).

Exclusion criteria were signs or symptoms of breast cancer, previous breast cancer (invasive or ductal in situ), cancer at any other site, presence of life-threatening diseases, known *BRCA* or *TP53* pathogenic germline mutation, and pregnancy. We also excluded women with general contraindications to MRI or to intravenous administration of gadolinium-based contrast agent; women who underwent hormonal enhancement of ovarian function for medically assisted reproduction in the previous three years; women planning a pregnancy; women undergoing postmenopausal hormone replacement therapy (HRT) who refused to suspend the treatment four weeks before MRI performance.

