### 2.7. Study Endpoints

The primary endpoint of this study was the rate of invasive and ductal in situ breast cancer detected in the two study arms. All breast cancers diagnosed as a consequence of an abnormality identified at the screening tests were considered screen detected.

Secondary endpoints included (1) the distribution of clinical and pathological stages of invasive breast cancers; (2) the histological characteristics of breast cancers; (3) the interval cancer rate, both between the two examinations and within one year from the second examination: any breast cancer (invasive or ductal in situ) diagnosed after a negative examination but before the following examination, scheduled approximately 1 year later, would be considered as an interval cancer; (4) the adherence to the assigned arm and any reason for consent withdrawal from the assigned program; (5) the distribution of the breast cancer risk profiles; (6) the number of breast cancers (invasive and in situ) detected in excess in the experimental arm compared to the conventional arm (overdiagnosis) after 4 years of follow up. The breast cancer risk profile was built combining the LTR score (<15% or ≥15%) and the BD at the most recent mammography before enrollment (ACR class *a* to *c*, or ACR class *d*), so that four risk categories (risk profile) were created: (1) LTR ≥ 15% and BD = *a* to *c*; (2) LTR < 15% and BD = *d*; (3) LTR ≥ 15% and BD = *d*; (4) LTR ≥ 15% and unknown BD.

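### The expected 40–60 cancers need five years of incidence, but their 1:2 split between arms needs detection by study screening, which lasts only two rounds

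*Protocol article*

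**What the plan says.** Section 2.8 sets the size of the feasibility trial ("a planned enrollment of 2000 women (10% of the size of the efficacy trial) was proposed") and then forecasts its yield: "over a 5-year screening period, about 40–60 cases of invasive breast cancer will be observed", with "one-third in the control arm; two-thirds in the MRI arm". It concludes that these numbers are enough to confirm a doubling of sensitivity with MRI, and to give preliminary information on lead time and stage distribution.

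The design sections describe a shorter screening phase:

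- Section 2.1: women are randomised "with a 1:1 allocation ratio" to annual screening, and "Two screening rounds per woman were planned".
- Section 2.5: after both rounds, women with negative or benign results go back to usual screening.
- Section 2.7: a secondary endpoint is "the interval cancer rate, both between the two examinations and within one year from the second examination", so the interval-cancer window closes about two years after the first examination.

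Five years appears elsewhere only as follow-up. The Abstract places the primary endpoint after five years of follow-up, and the end of section 2.8 plans clinical follow-up of at least that length. Section 2.7 defines the primary endpoint as the rate of invasive plus ductal in situ cancer, gives no time window, and then defines which cancers count as screen detected.

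**The concern.** The forecast refers to a five-year screening period that the design does not contain. This goes beyond a loose label, because the forecast has two parts that need different windows. A total of 40–60 needs five years of incidence. A 1:2 division between equal-sized randomised arms needs a count restricted to cancers that the study tests find, since cancers missed by mammography plus ultrasound will in large part surface later and be counted in the control arm.

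At stake are the statements in section 2.8 that lean on this forecast: confirmation of the sensitivity gain, and the preliminary information on lead time and stage. The trial is also meant to inform the size of an efficacy trial, so a reader may carry the forecast forward. In addition, the forecast counts invasive cancers only, while the primary endpoint includes ductal in situ cancers.

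**Working it through.** **Inputs from the article**

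- Planned size 2000, allocated 1:1, so 1000 per arm (sections 2.8 and 2.1).
- Ten-year breast cancer risk 5% on average, about 3% at the lowest (section 2.8). This is 0.5% and 0.3% per year.
- Two annual rounds, plus one year after the second: about 2 years (sections 2.1 and 2.7).
- Enrolled: 1254 (section 2.8).

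**Step 1. Reproduce the stated total.** Expected cancers = N × annual risk × years.

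- 2000 × 0.005 × 5 = 50, the midpoint of 40–60.
- The ends correspond to ten-year risks of 4% and 6%: 2000 × 0.004 × 5 = 40 and 2000 × 0.006 × 5 = 60.
- A constant-hazard calculation gives 50.6 instead of 50.

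The article does not print a derivation, so this is an inference, but it matches.

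**Step 2. Test the split against that total.**

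- With equal risk and 1:1 allocation, five-year incidence is 1000 × 0.005 × 5 = 25 per arm, apart from lead time and overdiagnosis.
- The stated split implies 40/3 to 60/3 = 13–20 in the control arm and 27–40 in the MRI arm.

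**Step 3. Two years of incidence.**

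| Women | 5% ten-year risk | 3% ten-year risk |
|---|---|---|
| 2000 | 2000 × 0.005 × 2 = 20 (16–24 at 4–6%) | 2000 × 0.003 × 2 = 12 |
| 1254 | 1254 × 0.005 × 2 = 12.5 | 1254 × 0.003 × 2 = 7.5 |

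**Step 4. Allow for prevalent cancers at round 1.** This needs assumptions that are not in the article: exponential preclinical (sojourn) time with mean S of 1–3 years, no earlier screening, and sensitivity 0.9 for MRI and 0.45 for mammography plus ultrasound. Per arm, with annual rate λ and sensitivity s:

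- found at round 1 = nλS × s;
- pool at round 2 = nλS(1 − s)e^(−1/S) + nλS(1 − e^(−1/S)), of which a fraction s is found.

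Example with n = 1000, λ = 0.005, S = 2:

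- MRI: 9.0 + 4.1 = 13.1.
- Mammography plus ultrasound: 4.5 + 3.3 = 7.8.

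| S (years) | Screen-detected: MRI / control / total | All cancers in 2 years | All cancers in 5 years: MRI / control |
|---|---|---|---|
| 1 | 7.5 / 4.1 / 11.6 | 22.7 | 25.1 / 25.0 |
| 2 | 13.1 / 7.8 / 20.9 | 29.4 | 26.3 / 25.8 |
| 3 | 18.3 / 11.3 / 29.6 | 37.1 | 28.8 / 27.5 |

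The two-round phase therefore yields about 12–30 screen-detected cancers, or 23–37 with interval cancers. The screen-detected ratio is 1.6–1.8, near the stated 1:2. The five-year ratio is close to 1, with a total of about 50–56.

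**Step 5. Five-year totals for the women enrolled.** 1254 × 0.005 × 5 = 31; at 3%, 1254 × 0.003 × 5 = 19.

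**Step 6. What the counts can show.** The article names no test. As an illustration, take an exact two-sided 5% binomial test of equal division when the truth is 1:2 (2/3 against 1/2):

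| Events | 20 | 40 | 50 | 60 |
|---|---|---|---|---|
| Power | 30% | 53% | 60% | 66% |

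**The case against.** The strongest reply is that the forecast speaks of cancers observed, not cancers detected by screening, and that the Abstract puts the primary endpoint after five years of follow-up. Women return to usual screening after round 2, so imaging does not stop at two years. On that reading about 50 is the right total for 2000 women. This stands for the total. It does not rescue the 1:2 split, which cannot be expected among all cancers to five years under 1:1 allocation.

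A reader might infer from the two-year figure of 20 that the count is overstated twofold or more. The documents do not support that. On the follow-up reading the total is not overstated. On the screening-phase reading, against the midpoint of 50, the factor is about 1.7–4.3 for screen-detected cancers (50/29.6 to 50/11.6) and 1.3–2.2 with interval cancers (50/37.1 to 50/22.7). It depends on sojourn time and sensitivities that the article does not give. That 95% of women had a pre-trial mammogram (section 4) points towards the higher factors but does not fix one.

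A reader might also infer that all of section 2.8 falls with this forecast. It does not: the target of 2000 was set as 10% of the efficacy trial, and the aims on specificity, risk profiles and organisation do not use the 40–60.

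Lastly, keeping a planning figure after "when 1254 women had been randomized, enrollment stopped due to the end of the grant" is not an arithmetic error. The shortfall is acknowledged in sections 4 and 5. The omission of in situ cancers works in the opposite direction, since adding them would raise the count.

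**Conclusion.** The point holds as an internal inconsistency. No single window and case definition in this design supports both the 40–60 total and the 1:2 split. The total is matched by five years of incidence at the article's 5% ten-year risk (50), which implies about 25 per arm. The split belongs to cancers found in a two-round phase of about two years, where incidence alone gives 20 (12 at 3%) and the illustrative model gives 12–37 depending on sojourn time and on whether interval cancers count.

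The claim of confirming a doubling of sensitivity is too strong on either basis: illustrative power is 53–66% at the stated 40–60 events and about 30% at 20. These conclusions assume equal underlying risk in the arms, a constant annual rate, and that the unprinted derivation is the one inferred here. The size of any overstatement cannot be fixed from the article.

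**What to change.** In section 2.8, replace the reference to five years of screening with the two planned rounds, and give two separate expectations, both using the primary endpoint's case definition (invasive plus ductal in situ):

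1. Cancers over the two-round phase, stating whether interval cancers are included and which sojourn time and sensitivities are assumed. The 1:2 split may be attached to this figure.
2. All cancers to five years of follow-up, without the 1:2 split. For invasive cancers this is about 50 in the 2000 planned, or about 31 (19 at 3% ten-year risk) in the 1254 enrolled, with in situ cancers to be added.

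Say which of the two corresponds to the primary endpoint. Reword the sensitivity statement to what those counts can support, for example an estimate with its precision instead of confirmation.

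The cost is a text correction. Enrolment and study screening are complete and nothing in the conduct of the trial changes; the stated yield simply becomes less favourable.

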## 3. Characteristics of Enrolled Patients

From July 2013 to November 2015, a total of 1254 women (mean age 47.2 ± 4.6 years) were enrolled: 624 were assigned to MX plus US (standard of care arm) and 630 to MRI (experimental arm). Table 2 reports the number of women recruited in each center, and their characteristics are detailed in Table 3.

Most women were below the age of 50 (72.2%) and premenopausal (44.6%) or perimenopausal (23.7%). More than one in four (27.6%) did not have children; 52.1% used oral contraceptives (currently or in the past); 15% of postmenopausal women had used HRT. Most women (86.3%) had a body mass index <25. Only 4.6% of enrolled women (58/1254) had their first breast examination in this trial, and most of them (44/58) were in their forties. Among women with a previous MX, an extremely dense breast at the most recent MX was recorded for 82.7% (984/1196). Breast and/or ovarian cancer in mothers and/or sisters was reported by 36.5% of enrolled women (458/1254) and 67 of them had a BC-LTR < 15%. A BC-LTR ranging from 15% to 30% was calculated for 41% (514/1254) of all enrolled patients, and 47.5% of them (244/514) also had a previous MX classified as extremely dense. Overall, 59% of enrolled women (740/1254) had, as a sole inclusion criterion, an extremely dense breast at MX (LTR < 15% and BD = *d*).

The distribution of major determinants of breast cancer risk profiles of women enrolled in the study varied across centers: the rate of women recruited on the basis of an MX classified as extremely dense ranged from 0% to 98.9% (Table 4).

The frequency of women reporting one or more first-degree relatives affected by breast and/or ovarian cancer ranged from 26.6% to 91.7%.

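### The expected cancer count does not support the stated ability to confirm a twofold increase with MRI, and it was not restated for the 1254 women enrolled

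*Protocol article*

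**What the plan says.** All of the relevant statements are in the protocol article.

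- Section 2.8 derives the size from a later efficacy trial: "a planned enrollment of 2000 women (10% of the size of the efficacy trial) was proposed". The twofold comparison played no part in setting it.
- Section 2.8 then gives the expected yield: "over a 5-year screening period", "about 40–60 cases of invasive breast cancer will be observed", divided "one-third in the control arm; two-thirds in the MRI arm". Section 2.1 randomises "with a 1:1 allocation ratio", so that division is a ratio of 2.
- On this basis Section 2.8 says that the figures "would enable us to confirm the twofold increase in sensitivity associated with MRI". No test, significance level, power or interval width accompanies the statement.
- The next paragraph of Section 2.8 reports that, "when 1254 women had been randomized, enrollment stopped due to the end of the grant". The expected count and the statement about confirmation are left as they were.
- Section 2.7 defines the primary endpoint as invasive plus ductal in situ cancers, whereas the 40–60 are invasive only. Section 2.1 plans two annual rounds.

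**The concern.** To say that a count is enough to confirm a doubling is to claim a capability. Section 2.8 itself separates what the counts can support (the doubling, and preliminary information on lead time and stage) from what they cannot (advanced cancers and deaths). If the power for a true doubling is modest, the comparison is on the wrong side of that line.

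The consequence lies in how the result is read. Outcome data are still to be published, and Section 5 hopes that they will help to plan an efficacy trial. A reader who takes the statement at face value could treat a non-significant difference as evidence against MRI, although such a result would be quite likely even if MRI truly doubled detection.

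**Working it through.** **Inputs from the article.** Expected invasive cancers 40–60 and a 1:2 split (Section 2.8); 1:1 allocation (Section 2.1); planned 2000 women (Section 2.8); enrolled 624 + 630 = 1254 (Section 3).

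**Assumptions.** The significance level is not stated for this comparison. Two-sided 5% is assumed, with one-sided 5% as a variant. The quantity tested is the ratio of detection counts. Each woman receives only her own arm's test, so there is no paired comparison of sensitivity. The ratio of detection rates stands in for the ratio of sensitivities if randomisation gives both arms the same underlying cancers.

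**Step 1: the article's own figures.** For the efficacy trial (25% reduction, 80% power), events = 4 × (1.960 + 0.842)² / (ln 0.75)² = 379.4, or 380 as stated. Two-sided 5% is therefore the level behind the one power statement in the article. The 40–60 cancers are consistent with 2000 × 5% × 5/10 = 50, although the article does not show that step.

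**Step 2: expected count at the enrolled size.** 1254/2000 = 0.627, a shortfall of 37%. Then 40, 50 and 60 become 25.1, 31.4 and 37.6, or about 25, 31 and 38.

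**Step 3: power for a true ratio of 2.**
- *Exact.* Given t cancers in total, the MRI count is Binomial(t, 1/2) under no difference and Binomial(t, 2/3) under a doubling. Reject when the upper tail is at most 0.025, and average over t ~ Poisson with the expected mean.
- *Normal approximation.* Power = Φ[(p₂ − p₁ − 1.96·SE₀)/SE₁], with SE₀ pooled and SE₁ unpooled. At 40 cancers and 1000 per arm: p₁ = 0.01333, p₂ = 0.02667, SE₀ = 0.00626, SE₁ = 0.00625, so Φ(0.170) = 57%. At 37.6 cancers with 624 and 630 women: p₁ = 0.0201, p₂ = 0.0398, SE₀ = 0.00963, SE₁ = 0.00960, so Φ(0.086) = 53%.

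| Size | Cancers | Exact | Normal approx. |
|---|---|---|---|
| Planned | 40 / 50 / 60 | 51 / 61 / 70% | 57 / 67 / 75% |
| Enrolled | 25 / 31 / 38 | 31 / 39 / 48% | 38 / 46 / 53% |

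Fisher's exact test gives 51–71% planned and 32–50% enrolled. A log-ratio (Schoenfeld) approximation gives 59–77% and 41–57%. The number of cancers needed for 80% power is about 66 by the log-ratio formula, 70–72 by the pooled normal or Fisher calculation, and 75 by the exact conditional test.

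**Step 4: variants that favour the plan (exact test).**
- One-sided 5%: 63–80% planned, 44–61% enrolled.
- Two-sided 5% with in situ cancers adding an assumed 15–30% to the count: 57–82% planned, 36–61% enrolled (normal approximation up to 85% and 65%).
- One-sided 5% and 30% added in situ cancers together: 74–89% planned, 55–72% enrolled.

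**Step 5: precision if the observed ratio is exactly 2.** With n cancers split n/3 and 2n/3, SE(ln ratio) = √(3/n + 3/(2n)) = √(4.5/n), and the interval is 2 × exp(±1.96 × SE). For n = 31, SE = 0.381.

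| Cancers | 95% CI |
|---|---|
| 40 / 50 / 60 (planned) | 1.04–3.86 / 1.11–3.60 / 1.17–3.42 |
| 25 / 31 / 38 (enrolled) | 0.87–4.59 / 0.95–4.22 / 1.02–3.93 |

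**The case against.** The strongest reply is that the sentence makes no claim of 80% power. It says that the expected figures would show a doubling, and at the planned size the expected split does exclude 1 (lower limits 1.04–1.17). That is correct, but it holds narrowly. A 27:13 split gives an exact two-sided p of 0.038, and moving one cancer to 26:14 gives 0.081. At the enrolled size the interval includes 1 at 25 and at 31 cancers.

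The second reply is that this is a feasibility trial whose shortfall is disclosed in Sections 4 and 5, and that Section 5 restates what the trial will deliver without mentioning the doubling. Sizing at a tenth of the efficacy trial is stated openly, and a detailed power calculation may sit in the full protocol. This lowers the severity. It does not rescue the sentence, because no section says what the shortfall does to this comparison.

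Three stronger readings are tempting, and the article does not support them.
- *At the enrolled size the trial has at best an even chance of showing a true doubling.* Normal approximations reach 53–57% at the top of the enrolled range, and the in situ and one-sided variants go higher.
- *80% power is out of reach under any reading.* The one-sided and in situ variants each reach it at the top of the planned range, and combining them reaches it lower in that range.
- *Two rounds in 1254 women would yield only some 10–17 cancers, with power of 11–20%.* The article gives no such count. Simple proration by time ignores prevalent cancers found at a first MRI round and the 5-year follow-up that the abstract attaches to the primary endpoint. The mismatch between a 5-year screening period and two rounds supports only the remark that the count may be lower.

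Nor does any section plan to read a non-significant result as evidence against MRI. That risk lies with the reader.

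**Conclusion.** The point stands in moderate form. The stated ability to confirm a doubling is not supported by the article's own counts, and those counts were not restated when enrolment ended 37% short. With a true ratio of 2 and an assumed two-sided 5% test, the chance of a significant result is roughly one-half to three-quarters at the planned size and three-tenths to just over one-half at the enrolled size, depending on the method and on where in the range the count falls. None of the one-sided or in situ variants examined reaches 80% at the enrolled size.

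The conclusion rests on three assumptions: the two-sided 5% level, simple pro rata scaling of the count to 1254 women, and the detection-count ratio as the quantity compared. It is a fault in a stated capability. It is not a fault in the randomised comparison, and it does not undermine the feasibility aims.

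**What to change.** In Section 2.8, or in the analysis plan and results report that follow from it:

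1. Replace the statement about confirming a doubling of sensitivity with one that the trial estimates the detection-rate ratio between arms with a 95% CI.
2. Restate the expected invasive count for 1254 women: about 25–38 pro rata, possibly fewer because the original count assumed five years of screening while two annual rounds were planned.
3. Give the expected interval if the ratio is 2: about 0.87–4.59 at 25 cancers, 0.95–4.22 at 31 and 1.02–3.93 at 38. If in situ cancers are added to match the primary endpoint, state the assumed proportion.
4. Say that a non-significant difference is not evidence of no difference.

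The cost is wording only. No women, examinations or data are added. The stated capability becomes less favourable.

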Our population comprised healthy women with a 2–3-fold increase in breast cancer risk, compared to a low-risk woman of the same age. We assessed BC-LTR with the IBIS Breast Cancer Risk Evaluation Tool version 6.0.0, which incorporates the most comprehensive set of personal risk factors and an extensive family history of breast and ovarian cancer. Since the IBIS Breast Cancer Risk Evaluation Tool does not integrate BD, we set extreme BD as an eligibility criterion. Over 70% of enrolled women were in their 40s, the age range in which screening recommendations are not consistent across Europe [42]. Due to recruitment at radiology units, 95% of enrolled women had a pre-trial MX, but the distribution of risk profiles varied widely across centers (from 0% to 99% of women having extremely dense breasts), showing different ultimate sources of recruitment (e.g., self-referral for breast examination or collaboration with familial cancer clinics for the surveillance of women at increased breast cancer risk who do not carry pathogenic germline variants). In our study, around one in four women with extreme BD had also a BC-LTR ≥ 15%: in this subgroup, a BC-LTR recalculation using the 2017 IBIS Breast Cancer Risk Evaluation Tool version 8b that includes BD in the model might take the risk over the 30% threshold in a high number of cases.

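### A 1:2 split of observed cancers between parallel arms is a detection-rate ratio and cannot by itself confirm a twofold sensitivity of MRI

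*Protocol article*

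**What the plan says.** Section 2.1 randomises women to "annual 2D MX plus US (standard-of-care arm) or MRI (experimental arm) with a 1:1 allocation ratio". It adds: "Two screening rounds per woman were planned".

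Section 2.7 makes the rate of invasive and ductal in situ cancers detected in each arm the primary endpoint. It defines screen-detected cancers. It also defines interval cancers, counted between the two examinations and within one year of the second, as a secondary endpoint. Another secondary endpoint labels the excess of cancers in the MRI arm as overdiagnosis.

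Section 2.8 states that "this feasibility trial aimed to estimate the sensitivity and specificity of MRI screening alone". It forecasts "about 40–60 cases of invasive breast cancer will be observed: one-third in the control arm; two-thirds in the MRI arm", and says that such figures "would enable us to confirm the twofold increase in sensitivity associated with MRI". The same paragraph expects the data to inform on MRI lead time, and notes: "Any estimation of the proportion of interval cancers in each arm proved to be difficult".

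On screening history, Section 3 says "Only 4.6% of enrolled women (58/1254) had their first breast examination in this trial", and the Discussion says "95% of enrolled women had a pre-trial MX".

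**The concern.** The text moves from a 1:2 split of cancers to a twofold sensitivity. That step is natural where the same women have both tests, because the two counts then share one set of cancers. The Discussion describes the observational background in those terms, as the gain from adding MX/US to MRI. In this trial the counts come from different women, and no shared set of cancers links them.

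The article itself gives two other readings of the same excess: lead time (Section 2.8) and overdiagnosis (Section 2.7). A third influence is screening before entry, which shapes the pool of cancers still to be found. One ratio cannot separate these.

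At stake is an interpretive claim. If the text is followed as written, a detection ratio near 2 could be published as a confirmed sensitivity ratio of 2.

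**Working it through.** **1. The plan's own figures.** Planned N is 2000 and the average 10-year risk is 5% (Section 2.8). Taking half the risk for five years gives 2000 × 0.05/2 = 50 cancers. Risks of 4% and 6% give 40 and 60, so the forecast reproduces. The split is 13.3:26.7 at 40 cancers and 20:40 at 60, a ratio of 2.0.

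**2. Inputs for the check.**
- From the article: the share with an earlier mammogram is 1196/1254 = 95.4%, and there are two annual rounds.
- Assumed, because the article gives none of them: sensitivities of 0.90 (MRI) and 0.60 (control), so a true ratio of 1.5; exponential preclinical duration with mean *m* = 1.5–3 years; earlier screens every 1–2 years with the control arm's sensitivity; one detectable phase common to both strategies.

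**3. One case by hand.** Take *m* = 1.5 and annual earlier screens, and scale the preclinical pool of a never-screened woman to 1. Then exp(−1/1.5) = 0.513, and new cancers per year are 1 − 0.513 = 0.487.

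*Misses persist (a tumour missed once stays missed).* The share of control-visible cancers left at entry is 1 − 0.954 × 0.513 = 0.510.
- Round 1: control 0.60 × 0.510 = 0.306; MRI 0.90 × (0.40 + 0.306) = 0.636; ratio 2.08.
- Round 2: control 0.60 × 0.487 = 0.292; MRI 0.90 × 0.487 = 0.438; ratio 1.50.
- Pooled: (0.636 + 0.438)/(0.306 + 0.292) = 1.80.

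*Misses are independent between screens.* The pool in previously screened women settles at 0.487/(1 − 0.40 × 0.513) = 0.612. Including the never-examined 4.6%, it is 0.954 × 0.612 + 0.046 = 0.630.
- Round 1: MRI 0.90 × 0.630 = 0.567; control 0.60 × 0.630 = 0.378; ratio 1.50.
- Round 2: MRI 0.90 × (0.10 × 0.630 × 0.513 + 0.487) = 0.467; control 0.60 × (0.40 × 0.630 × 0.513 + 0.487) = 0.370; ratio 1.26.
- Pooled: (0.567 + 0.467)/(0.378 + 0.370) = 1.38.

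The sensitivities, durations and screening history are identical in the two cases. Only the behaviour of misses differs, and it decides whether 1.5 is overstated or understated.

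**4. Range over the assumed inputs** (simulation; it agrees with the hand calculation to about 0.01):

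| True ratio | Misses | Round 1 | Pooled, two rounds |
|---|---|---|---|
| 1.5 (0.90 vs 0.60) | persist | 1.70–2.78 | 1.62–2.17 |
| 1.5 (0.90 vs 0.60) | independent | 1.50 | 1.32–1.38 |
| 2.0 (0.90 vs 0.45) | persist | 2.36–4.36 | 2.22–3.24 |
| 2.0 (0.90 vs 0.45) | independent | 2.0 | 1.64–1.77 |

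**5. A different model: MRI sees tumours for longer.** Assume a 3-year MRI-detectable phase, an MX+US window half as long, and sensitivities of 0.9 and 0.8. With one mammogram a year before entry, the pooled yield ratio is 2.26 against an interval-based sensitivity ratio of 1.35. With no earlier mammogram it is 1.92 against 1.26. On the log scale, ln(1.92/1.26)/ln(2.26/1.35) = 0.421/0.515 = 0.82. In this model about four fifths of the gap is therefore present without any earlier mammography.

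**The case against.** Several counter-arguments have force.

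- **The sentence is a remark on sample size, not an estimator.** The article never says that sensitivity will be computed as a ratio of counts, and a formula may sit in a fuller document. That is fair, so the absence of a formula is not the point here. The printed claim that these counts would confirm twofold sensitivity still stands as written.
- **Randomisation gives both arms the same expected pool at entry.** This holds. The round-1 ratio is a valid comparison of detection in this pre-screened population. It does not carry over to a count accumulated over more than one round, nor does it remove lead time and overdiagnosis.
- **The simulation covers two rounds, while the forecast is of cancers observed over five years.** This also holds, so the ranges are illustrations. It does not rescue the claim: if cancers that surface clinically are counted too, those missed by screening re-enter the count.

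A reader might go further and infer that earlier mammography makes the plan overstate MRI sensitivity, by setting a first-ever MRI against a repeat mammogram. The documents do not support that:

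- The upward direction needs persistent misses or a longer MRI-detectable phase. The Introduction's statement on masking, with 79% extremely dense breasts, makes this plausible but not established.
- At most the MRI:control ratio is affected, not MRI's own sensitivity.
- Earlier MRI is neither reported nor excluded. Earlier ultrasound and time since the last mammogram are not given.

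Nor would a wrong sensitivity ratio upset the efficacy-trial size in Section 2.8. That rests on a 25% mortality reduction, 5% risk and 60% survival: 20,000 × 0.05 × 0.40 = 400 deaths, against the 380 required.

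**Conclusion.** The point holds in a limited form. The 1:2 split forecast in Section 2.8 is a detection-rate ratio, and in a parallel-arm design it does not identify the MRI:control sensitivity ratio. For a true ratio of 1.5, the assumed models give pooled yield ratios from 1.32 to 2.17, so a twofold yield can arise without twofold sensitivity. Conversely, with independent misses a true twofold sensitivity can show as 1.64–1.77.

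These ranges rest on assumed sensitivities, preclinical durations and earlier screening intervals. The documents fix neither the size nor the direction of the gap. The primary endpoint and its randomised comparison are unaffected.

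**What to change.** - Delete or reword the statement that the count split would confirm twofold sensitivity, and describe the split as an expected detection-rate ratio.
- Estimate sensitivity within each arm as screen-detected/(screen-detected + interval cancers within 12 months), with exact confidence intervals. Both components are already defined in Section 2.7. The difficulty noted in Section 2.8 concerns forecasting the interval-cancer proportion and does not prevent estimating it from observed data. State that this measure too can be raised by overdiagnosed cancers in the numerator.
- Report yields separately for round 1 (equal expected pools by randomisation, in a largely pre-screened cohort) and round 2. Do not present round 2 as like-for-like, because the arms' remaining pools differ once round 1 has been done.
- Do not add an analysis excluding the 58 women with no earlier breast examination. It would leave a wholly pre-screened cohort and could not reduce the problem.

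The cost is a change of wording and a few tables from data already planned. The downside is imprecision: 9 of 10 cancers screen-detected gives an exact 95% interval of 55.5% to 99.7%.
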